## Methods/Design

### Overview

APACHE-AF (Fig. 1, http://www.apache-af.nl) is a phase II, randomised, open-label, parallel-group, multicentre clinical trial with masked outcome assessment (PROBE design [44]), comparing apixaban and avoiding anticoagulation in patients with AF and a recent anticoagulation-associated ICH. An adjudication committee blinded to treatment allocation will adjudicate outcomes.

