### Study outcomes

The primary outcome is the combination of vascular death or non-fatal stroke (cerebral infarction, ICH, or subarachnoid haemorrhage) during follow-up. Secondary outcomes will be: vascular death, death from any cause, all stroke, ischaemic stroke, ICH, other major extracranial haemorrhage, any intracranial haemorrhage other than ICHd, systemic embolism, myocardial infarction, and functional outcome as assessed with the score on the mRS at 6 and 12 months; annually thereafter; and at the end of the study. Definitions of the clinical events comprising the study outcomes are shown in Table 3.

**Table 3 Tab3:** Event definitions

Ischaemic stroke	Clinical evidence of the sudden onset of a new neurological deficit, or an increase in an existing deficit, persisting for more than 24 hours, without evidence of a intracerebral haemorrhage on a CT or MRI scan or at post-mortem investigation
Intracerebral haemorrhage	Clinical evidence of the sudden onset of a new neurological deficit, or an increase in an existing deficit, persisting for more than 24 hours, with a corresponding intracerebral haemorrhage on a CT or MRI scan or at post-mortem investigation
Unclassified stroke	Clinical evidence of the sudden onset of a new neurological deficit, or an increase in an existing deficit, persisting for more than 24 hours, without imaging or post-mortem investigations performed
Subarachnoid haemorrhage	Subarachnoid haemorrhage (SAH) demonstrated by CT, lumbar puncture, or at post-mortem investigation
Myocardial infarction	Evidence of myocardial necrosis in a clinical setting consistent with acute myocardial ischemia. Under these conditions any one of the following criteria meets the diagnosis for MI [51]:
	● Detection of a rise and/or fall of cardiac biomarker values (preferably cardiac troponin) with at least one value above the 99th percentile upper reference limit and with at least one of the following:
	○ Symptoms of ischemia
	○ New or presumed new significant ST-segment-T wave changes or new left bundle branch block (LBBB)
	○ Development of pathological Q waves in the ECG
	○ Imaging evidence of new loss of viable myocardium or new regional wall motion abnormality
	○ Identification of an intracoronary thrombus by angiography or autopsy
	● Cardiac death with symptoms suggestive of myocardial ischemia and presumed new ischemic ECG changes or new LBBB, but death occurred before cardiac biomarkers

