Vascular death	Death from cerebral infarction; intracerebral, subarachnoid, epidural, or subdural haemorrhage; unclassified stroke; myocardial infarction; extracranial haemorrhage; or systemic embolism, fatal arterial or gastric bleeding, terminal heart failure, fatal pulmonary embolism, and sudden death, defined as death within 1 hour after onset of symptoms
Major extracranial haemorrhage	Major extracranial bleeding will be defined using the ISTH criteria [52];
	1) Fatal bleeding, and/or
	2) Symptomatic bleeding in a critical area or organ, such as intraspinal, intraocular, retroperitoneal, intra-articular or pericardial, or intramuscular with compartment syndrome, and/or
	3) Bleeding causing a fall in haemoglobin level of 1.24 mmol L^−1^ or more, or leading to transfusion of 2 or more units of whole blood or red cells
Clinically relevant non-major bleeding	Clinically relevant non-major bleeding will be defined as acute clinically overt bleeding that does not satisfy additional criteria required for the bleeding event to be defined as a major bleeding event and meets at least one of the following criteria [53]:
	● Hospital admission for bleeding
	● Physician-guided medical or surgical treatment for bleeding
	● Change in antithrombotic (anticoagulant or antiplatelet) therapy
Intracranial haemorrhage	Intracerebral haemorrhage (see above), SAH (see above), subdural haemorrhage: evidence of a subdural haematoma on a CT or MRI scan or at post-mortem investigations; epidural haematoma: evidence of an epidural haematoma on a CT or MRI scan or at post-mortem investigations
Systemic embolism	The diagnosis of systemic embolism requires a clinical history consistent with an acute loss of blood flow to a peripheral artery (or arteries) supported by evidence of embolism from surgical specimens, post-mortem investigations, angiography, vascular imaging, or other objective testing

*CT* computed tomography, *ECG* electrocardiogram, *MRI* magnetic resonance imaging

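### Subarachnoid haemorrhage is the only stroke type in Table 3 with no clinical criterion, so a symptomless finding counts as a primary-outcome stroke

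*Protocol article*

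**What the plan says.** The Study outcomes section states: "The primary outcome is the combination of vascular death or non-fatal stroke (cerebral infarction, ICH, or subarachnoid haemorrhage) during follow-up". It refers to Table 3 for the event definitions.

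In Table 3 the whole SAH row reads "Subarachnoid haemorrhage (SAH) demonstrated by CT, lumbar puncture, or at post-mortem investigation". The other stroke rows start from clinical evidence of an abrupt new or increased deficit and then add:

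- ICH: "persisting for more than 24 hours, with a corresponding intracerebral haemorrhage on a CT or MRI scan or at post-mortem investigation"
- Ischaemic stroke: "persisting for more than 24 hours, without evidence of a intracerebral haemorrhage on a CT or MRI scan or at post-mortem investigation"
- Unclassified stroke: "persisting for more than 24 hours, without imaging or post-mortem investigations performed"

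The intracranial haemorrhage row covers ICH and SAH by pointing back to their own rows, and adds epidural and subdural bleeds, the latter as "subdural haemorrhage: evidence of a subdural haematoma on a CT or MRI scan". Intracranial haemorrhage other than ICH is a secondary outcome. The vascular death row includes death from SAH and from subdural or epidural haemorrhage.

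On ascertainment, the Overview describes open-label treatment with masked outcome assessment. Under Study procedures, the treating physician or a representative carries out the follow-up visits, and images from routine care are collected for central reading. Under Outcome adjudication, a committee of two neurologists and a cardiologist works blinded to allocation.

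**The concern.** For three stroke types, the deficit requirement keeps chance findings on a scan out of the count. The SAH row has no such filter and asks for no symptoms at all. A patient who is scanned after a fall and has a trace of subarachnoid blood, but no illness from it, therefore meets the primary outcome.

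Two things are at stake. First, the trial exists to estimate the primary event rate in each arm for a phase III design, and events that are not clinically strokes would raise that rate. Second, whoever decides to scan knows the allocation. If the threshold for scanning differs between patients on apixaban and those avoiding anticoagulation, the extra events could fall unevenly. The same outcome also feeds the interim comparisons by the data monitoring board.

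**Working it through.** **Step 1. Set the rows side by side (Table 3).**

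| Row | Clinical criterion | Evidence accepted | Trauma addressed |
|---|---|---|---|
| Ischaemic stroke | deficit, over 24 h | no ICH on CT, MRI or post-mortem | no |
| ICH | deficit, over 24 h | CT, MRI or post-mortem | no |
| Unclassified stroke | deficit, over 24 h | none performed | no |
| SAH | none | CT, lumbar puncture or post-mortem | no |
| Subdural, epidural | none | CT, MRI or post-mortem | no |

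SAH is the only stroke row with an empty clinical column. In that respect it is written like the subdural and epidural entries, yet a non-fatal subdural or epidural bleed is not a primary event and a non-fatal SAH is. Trauma is not addressed in any row. MRI is named for ICH, subdural and epidural bleeds but not for SAH.

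**Step 2. Apply the text to a case.** Suppose a patient falls and has a CT scan that shows both a small SAH and a small subdural haematoma, with no symptoms from either, and survives. The SAH meets its row and is a primary event. The subdural counts only under the secondary outcome. Blinded reading can confirm that blood is present, but the SAH row contains no further condition to test.

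**Step 3. Reproduce the plan's own figure.** Sample size estimation gives 10 events in 100 patient-years with a 95% CI of 4.9 to 17.6. The exact binomial interval for 10/100 is 4.90 to 17.62, which matches. (The exact Poisson interval is 4.80 to 18.39.) Follow-up under uniform accrual without loss is 50 × (30/2 + 12)/12 = 112.5 patient-years per arm, in line with the stated figure of about 100. The point about the definition does not depend on these numbers.

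**Step 4. Scale, as an illustration only.** Assumption: 10 events per 100 patient-years in each arm, plus k extra symptomless SAHs in one arm. The article gives no value for k. Rate ratio = (10 + k)/10, with 95% CI = ratio × exp(±1.96 × √(1/(10 + k) + 1/10)).

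| k | Rate per 100 patient-years | Rate ratio | 95% CI |
|---|---|---|---|
| 0 | 10 | 1.00 | 0.42 to 2.40 |
| 1 | 11 | 1.10 | 0.47 to 2.59 |
| 2 | 12 | 1.20 | 0.52 to 2.78 |
| 3 | 13 | 1.30 | 0.57 to 2.96 |

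Each extra event adds 1 per 100 patient-years, or 1/10 = 10% of the assumed rate. The intervals show that a shift of this size is small beside sampling error.

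**The case against.** The strongest case against the point has four parts.

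1. **Scans need a trigger.** The visits described include no scan, so most imaging would follow symptoms or an injury. Every participant has had a recent anticoagulant-related ICH, and comparator patients may take antiplatelet drugs, so a low threshold for scanning is plausible in both arms. This stands as a limit on the concern. A reader might infer that the design produces biased detection, but the article does not show that. It shows only that the decision to scan is unmasked. Blinded adjudication and central reading protect in part, but they cannot supply scans that were never made.

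2. **Adjudicators may use judgement.** The component is called stroke, the assessors are experienced, and fuller adjudication instructions may exist. That is possible. However, Table 3 is presented as the event definitions and its SAH row is complete as it stands, so the stated rule admits the event.

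3. **A lasting focal deficit is the wrong test for SAH.** This is a fair reason not to copy the 24-hour rule. It is not a reason to have no clinical criterion at all.

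4. **The comparison can be overdrawn.** A reader might infer that SAH alone lacks a trauma exclusion, but none of the stroke rows has one. A reader might call SAH an imaging-only event, but lumbar puncture and post-mortem also qualify. The contrast with subdural haematoma holds only for non-fatal bleeds, since a fatal subdural is a vascular death. Leaving out MRI narrows the SAH count, so it is a separate inconsistency and not a source of over-counting.

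**Conclusion.** The point holds in a limited form. The SAH row is the only stroke definition without a clinical criterion and, followed literally, it lets symptomless bleeds into the primary outcome. This follows from the text and needs no assumption.

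Uneven detection by arm is a plausible risk that rests on two facts, open-label treatment and imaging from routine care. It is not demonstrated.

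The size is unknown. A reader might take the 10 events per 100 patient-years as the planned rate and a ratio of 1.2 as the expected distortion. The article supports neither reading: it says that reliable rate estimates are lacking, uses 10 events only to show the width of an interval, and gives no SAH frequency. The effect may well be nil. This is a minor correction, worth making because it is cheap and because the rate itself is what the trial is meant to deliver.

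**What to change.** Edit two rows of Table 3 together, and the adjudication form to match.

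- **SAH row, for the primary outcome:** require corresponding acute clinical symptoms, not necessarily a focal deficit lasting 24 hours, with SAH shown by CT, MRI, lumbar puncture or post-mortem.
- **Trauma:** state one rule and apply it to both SAH and ICH, so that the change does not create a new inconsistency between them.
- **Intracranial haemorrhage row:** replace the cross-reference to the SAH row with any SAH shown by CT, MRI, lumbar puncture or post-mortem. Without this second edit, narrowing the SAH row would also drop the excluded bleeds from the secondary outcome.
- **Vascular death row:** keep death from SAH where it is.

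Recruitment has begun, so the new wording should be settled without sight of results by arm, and any SAH already adjudicated should be reviewed against it under blinding.

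The cost is a short amendment. The downside is that a few bleeds may move from the primary to a secondary outcome. Accepting MRI could bring in a symptomatic SAH that the present row would miss.

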**Inclusion criteria**
Intracerebral haemorrhage (including isolated spontaneous intraventricular haemorrhage), documented with CT or MRI, during treatment with anticoagulation (VKA, any direct thrombin inhibitor, any factor Xa inhibitor, or (low-molecular-weight) heparin at a therapeutic dose)
The haemorrhage has occurred between 7 and 90 days before randomisation
Diagnosis of (paroxysmal) non-valvular AF, documented on electrocardiography
A CHA_2_DS_2_-VASc score ≥ 3
Score on the modified Rankin Scale (mRS) [45]
Equipoise regarding the optimal medical treatment for the prevention of stroke. The clinical equipoise should be self-reported by the attending neurologist after reviewing all relevant information available for the individual patient
Age ≥ 18 years
Written informed consent by the patient or by a legal representative

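### Table 3's Intracranial haemorrhage row requires a deficit of more than 24 hours for parenchymal bleeding but not for other compartments, so some new bleeds fall in no listed bleeding outcome

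*Protocol article*

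**What the plan says.** All of this is in the protocol article. Study outcomes lists the secondary outcomes and refers to Table 3 for the event definitions. The bleeding outcomes in that list are "ICH, other major extracranial haemorrhage, any intracranial haemorrhage other than ICHd, systemic embolism, myocardial infarction" (the last two items are not bleeding outcomes, and the final letter of ICHd appears to be a typographical slip).

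Table 3 then defines the events:

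- ICH: a new or increased deficit "persisting for more than 24 hours, with a corresponding intracerebral haemorrhage on a CT or MRI scan or at post-mortem investigation".
- Subarachnoid haemorrhage: "Subarachnoid haemorrhage (SAH) demonstrated by CT, lumbar puncture, or at post-mortem investigation".
- Intracranial haemorrhage: "Intracerebral haemorrhage (see above), SAH (see above), subdural haemorrhage: evidence of a subdural haematoma on a CT or MRI scan" or at post-mortem, and then "epidural haematoma: evidence of an epidural haematoma on a CT or MRI scan or at post-mortem investigations".

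The Intracranial haemorrhage row is a closed list of four types. Only the first, through its cross-reference, needs a clinical deficit. Intraventricular bleeding is not named in it or anywhere else in Table 3. The inclusion criteria in Table 1, by contrast, describe the index event as "Intracerebral haemorrhage (including isolated spontaneous intraventricular haemorrhage), documented with CT or MRI", with no minimum duration of deficit.

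**The concern.** Requiring a lasting deficit is a reasonable way to define ICH as a type of stroke. The difficulty is that the same requirement is carried into a row about bleeding inside the skull, and there it applies to one compartment only. A subdural haematoma found by chance counts. A new parenchymal bleed that causes a seizure, a headache or a deficit clearing within a day does not, even with a scan that proves it.

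Parenchymal bleeding is the event that brings nearly all patients into this trial, and the Interim analyses section names ICH among the main outcomes for harm. Comparing recurrent ICH and other major haemorrhage is a stated secondary objective, and the trial exists to inform a phase III design. An intracranial bleeding rate that omits part of the most relevant type is a weaker input to that design.

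**Working it through.** **Step 1. Trace each type of non-fatal bleed through Table 3 and the outcome list.**

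- Parenchymal, deficit over 24 hours: meets the ICH row. Counted as ICH, as intracranial haemorrhage and in the primary outcome.
- Parenchymal, no deficit over 24 hours: fails the ICH row, and so fails the first item of the Intracranial haemorrhage row. It is not subarachnoid, subdural, epidural or extracranial. No listed bleeding outcome.
- Isolated intraventricular, deficit over 24 hours: ICH if the Table 1 usage carries over. If Table 3 is read literally without it, there is a lasting deficit and no intracerebral haemorrhage on the scan. That meets the ischaemic stroke row. The event stays in the primary composite but is coded as the wrong type.
- Isolated intraventricular, no deficit over 24 hours: no listed bleeding outcome on either reading.
- Subarachnoid, subdural or epidural: counted on demonstration alone, with no deficit needed.

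**Step 2. Look for another place that would catch the second and fourth types.**

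- Clinically relevant non-major bleeding (Table 3) is not restricted to extracranial sites. It would fit an overt bleed that led to admission, treatment or a change of antithrombotic drug. It is not among the listed outcomes; its one stated use is in the footnote to the exclusion criteria.
- Safety reporting sends suspected haemorrhagic adverse events and all SAEs to the sponsor, and Statistical analysis compares SAEs by arm. The events are therefore known, but this route pools them with other events and gives no intracranial bleeding rate.

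**Step 3. Size per missed bleed.** The one precision figure in Sample size estimation is a 95% CI of 4.9 to 17.6 for ten primary events in 100 patient-years. It reproduces as an exact binomial interval for 10/100 (4.90 to 17.62). It concerns the primary outcome and does not enter this point. Only the denominator of about 100 patient-years per arm is used here.

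With k missed bleeds in an arm, the shortfall in its rate is k / 100 patient-years. The article gives no value for k. Taking k from 0 to 3 as an assumption, with exact Poisson 95% limits per 100 patient-years:

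- k = 0: shortfall 0 (0 to 3.7)
- k = 1: shortfall 1 (0.03 to 5.6)
- k = 2: shortfall 2 (0.2 to 7.2)
- k = 3: shortfall 3 (0.6 to 8.8)

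For scale only, the Background cites annual recurrent ICH risks of 2.3% to 8.2%. Treated as rates, these give 2.3 to 8.2 bleeds per 100 patient-years, so one bleed equals between 1/8.2 = 12% and 1/2.3 = 43% of such a count. That range comes from small observational studies of ICH survivors on acetylsalicylic acid or no antithrombotic drug, so it is not a forecast for either arm.

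**Step 4. Effect on the comparison.** If the same fraction f is missed in both arms, the observed rates are (1 − f)λ₁ and (1 − f)λ₂. Their ratio is λ₁/λ₂, as before, and both absolute rates are too low by the fraction f.

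**The case against.** The best defence is that the row is a closed list serving a secondary outcome, that a lasting deficit matches the other clinical stroke rows, and that one definition is applied to both arms by a blinded committee. Most of this stands. It supports the ICH row as a stroke definition and removes any presumption of differential bias. It does not explain why, within a single row, one compartment needs a deficit and the other three do not.

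Several stronger conclusions are tempting, and the article does not support them.

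- A reader might infer that isolated intraventricular bleeding is never counted. Table 1 treats it as a form of ICH, so with a lasting deficit it is ICH on the ordinary reading. The fair criticism is that Table 3 does not repeat this.
- A reader might infer that these bleeds are lost to safety monitoring. They are reportable as haemorrhagic adverse events, and those that are SAEs are compared by arm.
- A reader might infer that the gap favours apixaban. Ethical considerations expects more bleeding with apixaban or an antiplatelet drug, and antiplatelet drugs are allowed in the comparator arm, so that statement does not rank the arms.
- A reader might put a percentage on the missed bleeds. The article gives none; any share would be an assumption. No scheduled follow-up scan is described, so truly silent bleeds would mostly go undetected under any definition. The practical gap is bleeds that are scanned in routine care.

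**Conclusion.** The inconsistency is real and follows from the text alone. A non-fatal, scan-proven new parenchymal or isolated intraventricular bleed without a deficit over 24 hours is in no listed bleeding outcome, while a symptom-free subdural, epidural or subarachnoid bleed is. The secondary intracranial bleeding rates can therefore be too low in both arms, by about 1 per 100 patient-years for each bleed missed in an arm. That figure rests on the article's own estimate of about 100 patient-years per arm. How many bleeds would be missed, and whether the arms would differ, cannot be determined.

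The missing intraventricular wording in Table 3 is a smaller, separate point: it leaves room for a bleed to be coded as an ischaemic stroke.

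This is a worthwhile correction to a secondary safety outcome. It is not a reason to change the primary outcome.

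**What to change.** 1. Keep the clinical ICH definition, with its deficit of more than 24 hours, for the stroke and primary outcomes.
2. Reword the Intracranial haemorrhage row along these lines: *any new bleeding into the brain tissue or ventricles shown on CT, MRI or at post-mortem, whatever the kind or duration of symptoms; subarachnoid, subdural and epidural bleeding by their present criteria.* Do not add a symptom requirement to the row, since that would remove symptom-free bleeds that count now.
3. Report all intracranial haemorrhage as a secondary safety outcome. Assign bleeds that fail the ICH stroke row to the existing outcome "any intracranial haemorrhage other than ICHd", and label that outcome so that it is clear it can hold parenchymal bleeds.
4. State in the ICH row that isolated intraventricular haemorrhage is included, to match Table 1.

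The cost is new wording in two rows and one outcome label, with a matching change to the adjudication form. Suspected haemorrhagic events already reach the sponsor, so no new data collection is needed. The small downside is that a few mild or incidental bleeds enter the safety outcome, and its rate will be slightly higher.

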### Outcome adjudication

An outcome adjudication committee will adjudicate new outcomes on a regular interval. This committee will consist of two experienced vascular neurologists and an experienced cardiologist. The committee will receive outcome information blinded to patient identifiers and treatment allocation.

### Sample size estimation

For the population under study, there are no reliable estimates of the occurrence of the primary outcome for each of the tested treatments, and the main aim of this study is, therefore, to obtain such estimates to inform the design of a phase III clinical trial. Inclusion of a total of 50 patients in each of the treatment arms during the first 30 months of the study and 1 final year of follow-up will result in about 100 patient-years of follow-up in each treatment arm. Ten primary outcome events in 100 patient-years of follow-up will yield a 95 % CI of 4.9 to 17.6. This estimate will not only be more reliable because selection bias will not play a major role in this phase II trial, but also be more precise in comparison with the previous retrospective cohort studies.

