### Statistical analysis

The primary analysis will be based on the intention-to-treat principle. As a secondary analysis, we will perform a per-protocol analysis for the primary study outcome. Before the end of the study, a final statistical analysis plan will be completed.

The occurrence of the primary outcome (occurrence of vascular death or a non-fatal stroke) in each of the 2 treatment groups will be expressed as an annual event rate with a 95 % CI. The occurrence of the primary outcomes between the 2 treatment groups will be reported in terms of the hazard ratio with corresponding 95 % CIs, calculated with the Cox proportional hazard model.

The effect of the allocated treatment on the various other outcome events and SAEs will be assessed in the same fashion as the primary study parameter.

We will dichotomise the mRS scores at follow-up into 3 to 6 (poor outcome) and 0 to 2 (good outcome). The effect of the treatment on the mRS will be analysed using risk ratios with a corresponding 95 % CI.

We will adjust the crude hazard ratios and risk ratios for possible baseline incomparability given the size of the study.

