### Interim analyses

Interim analyses on safety and efficacy will be performed by the Data Safety and Monitoring Board (DSMB) according to the DSMB charter. These analyses are performed after 50, 100, and 150 patient-years of follow-up, and ad hoc as needed.

The interim analyses on both safety and efficacy will be performed on the primary outcome: the occurrence of vascular death or non-fatal stroke. This combined outcome consists of both the main efficacy outcome (ischaemic stroke) events as well as the main outcomes for harm (ICH, fatal vascular event).

The DSMB will compare both treatment arms using a Poisson’s test (Conditional Test) with two-sided testing. For all interim analyses of the primary outcome, a boundary of *P* < 0.01 will be used for any recommendation to terminate the trial.

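### The interval 4.9 to 17.6 that supports the sample size is a binomial interval for 10 of 100 patients, not an interval for 10 events in 100 patient-years

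*Protocol article*

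**What the plan says.** The Sample size estimation section explains that reliable event rates for this population are lacking, and that "the main aim of this study is, therefore, to obtain such estimates to inform the design of a phase III clinical trial". The size rests on exposure: enrolling 50 patients per arm over 30 months, then observing everyone for one more year, is expected to be enough and "will result in about 100 patient-years of follow-up in each treatment arm". The precision expected from this is then given in one sentence: "Ten primary outcome events in 100 patient-years of follow-up will yield a 95 % CI of 4.9 to 17.6". Neither a unit nor a method accompanies the interval, and the section contains no power calculation or other precision figure.

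Two other sections show how the same outcome is treated elsewhere. Under Statistical analysis, the primary outcome in each group "will be expressed as an annual event rate with a 95 % CI". Under Interim analyses, the data monitoring board compares the arms on the same outcome with a Poisson "test (Conditional Test) with two-sided testing".

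**The concern.** The sentence gives an event count over person-time. The natural model for that is a Poisson count with known exposure, and the protocol adopts this framework itself at the interim analyses. A binomial interval with a denominator of 100 instead assumes 100 separate subjects, each of whom either has the event or does not. Each arm has only 50 patients, followed for between 1 year (the last enrolled) and 3.5 years (the first enrolled: 2.5 years of accrual plus 1 year). Patient-years have been treated as if they were patients.

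The trial is sized for estimation, so this interval is its whole quantitative justification, and phase III planners will read it as the precision to expect. The upper limit matters most to them, because it bounds how high the event rate could plausibly be, and that is where the printed figure departs most from the exact interval for a rate.

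**Working it through.** **Inputs.** From Sample size estimation: x = 10 events, T = 100 patient-years, 50 patients per arm, 95% confidence (taken as two-sided, 2.5% in each tail). From Statistical analysis: the target is an annual event rate.

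**Step 1. Reproduce the printed figure.** Clopper-Pearson for x = 10, n = 100:

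- lower = Beta quantile(0.025; 10, 91) = 4.90%
- upper = Beta quantile(0.975; 11, 90) = 17.62%

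Rounded, this is 4.9 to 17.6, which matches both printed limits.

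**Step 2. Compute the exact interval for a rate.** For a Poisson count of 10 over 100 patient-years:

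- lower = χ²(0.025; 20 df)/2 = 9.591/2 = 4.795
- upper = χ²(0.975; 22 df)/2 = 36.781/2 = 18.390

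The interval is 4.8 to 18.4 per 100 patient-years.

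**Step 3. See whether another interval could explain the printed limits.**

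| Method | Lower | Upper |
|---|---|---|
| *Printed* | 4.9 | 17.6 |
| **Rate intervals** | | |
| Poisson exact | 4.80 | 18.39 |
| Byar | 4.79 | 18.39 |
| Poisson mid-P | 5.08 | 17.82 |
| Poisson Jeffreys | 5.14 | 17.74 |
| Poisson score | 5.43 | 18.41 |
| Log-rate Wald | 5.38 | 18.59 |
| Square-root transform | 4.76 | 17.16 |
| Plain Wald | 3.80 | 16.20 |
| **Binomial intervals, n = 100** | | |
| Clopper-Pearson | 4.90 | 17.62 |
| Wilson | 5.52 | 17.44 |
| Wilson, continuity-corrected | 5.16 | 18.04 |
| Agresti-Coull | 5.35 | 17.61 |
| Jeffreys | 5.26 | 17.01 |
| Logit | 5.47 | 17.60 |

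Only Clopper-Pearson gives both printed limits. No interval for a rate does.

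**Step 4. Check the tail probabilities.** If 4.9 and 17.6 were exact 95% limits for a Poisson mean, each tail would be 0.025. Instead P(X ≤ 10 | mean 17.6) = 0.037 and P(X ≥ 10 | mean 4.9) = 0.028. Under a binomial with n = 100 and p = 0.176, P(X ≤ 10) = 0.0253, which is what the exact binomial method would produce.

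**Step 5. Size of the discrepancy.**

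- Upper limit: 18.4 − 17.6 = 0.8 per 100 patient-years too low as printed
- Lower limit: 4.9 − 4.8 = 0.1 too high as printed
- Width: 18.39 − 4.80 = 13.6 against 17.6 − 4.9 = 12.7; ratio 13.595/12.7 = 1.07

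At a rate of 10 per 100 patient-years, about 113 patient-years per arm would be needed for the exact Poisson interval to be as narrow as the printed one (5.05 to 17.76, width 12.71).

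**The case against.** The case for leaving the figure alone has four parts.

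- **The difference is small and the scenario illustrative.** Ten events is a round example, exposure is given only as approximately 100 patient-years, and no target width was set from which 50 per arm was solved. This is right, and it limits the consequence. It does not make the printed limits correct.
- **Overstated precision depends on the comparator.** Exact Poisson limits are conservative. Mid-P Poisson limits have about the printed width (12.7), and Jeffreys (12.6), square-root and plain Wald (both 12.4) are slightly narrower. This stands as a qualification: the 7% is relative to the exact interval. That is nonetheless the like-for-like comparison, because the printed interval is itself exact, only for the wrong distribution.
- **Real exposure may exceed 100 patient-years.** With uniform accrual over 30 months, one further year and no deaths or losses, an arm yields 50 × (1.25 + 1) = 112.5 patient-years. Eleven events in that time give an exact Poisson interval of 4.9 to 17.5 per 100 patient-years, almost the printed one. This is a best case, since deaths and losses reduce exposure, and it describes a different count and exposure from those in the sentence.
- **Nothing shows that the final analysis will repeat the error.** The Statistical analysis section commits to a rate, the interim test is Poisson, and the interval method can properly be left to the statistical analysis plan. This stands. The finding concerns the stated figure only.

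The qualitative claim that the trial will be more precise than the retrospective cohorts is also untouched by a shift of this size.

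**Conclusion.** The printed interval is wrong for the quantity it describes. It is the exact binomial interval for 10 of 100 subjects; the exact interval for 10 events in 100 patient-years is 4.8 to 18.4 per 100 patient-years. Identifying the source rests on both limits matching Clopper-Pearson and matching none of the other intervals tried. The size of the error rests on taking exact Poisson limits as the comparator and on the protocol's own inputs of 10 events and 100 patient-years. On that basis precision is overstated modestly, almost entirely at the upper end. The choice of 50 per arm survives. The figure should still be corrected, because the trial's stated purpose is to estimate these rates and no other number supports its size.

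**What to change.** In Sample size estimation, replace the interval with a statement that ten events in 100 patient-years correspond to a rate of 10 per 100 patient-years, with an exact Poisson 95% CI of 4.8 to 18.4 per 100 patient-years. Giving the unit and the method in the same sentence removes the ambiguity. The cost is one corrected figure and a slightly less favourable stated precision; design, conduct and patient numbers do not change. When the statistical analysis plan is written, it would be sensible to name a person-time method for the per-arm rate intervals so that the two agree, but the correction does not depend on this.
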